The school principal was contacted by the study team to inform of random allocation. This is necessary as the principal and other staff have to negotiate placing of intervention materials, changes in physical environment, etc. The staff are informed about whether they are intervention or control schools but they are requested not to inform the students prior to baseline, but instead leave all communication regarding the study to the research group.

### Materials and procedures

Through the conduct of our acceptability and feasibility trial [20], we developed and tested many of the instruments and data collection methods that are used in the trial described in this protocol. Data is collected from students at four time points: pre-intervention baseline (Time 1, T1), during intervention after the 3rd intervention session (T2, intervention arm only), post-intervention at 2 months (T3), and at 14 months (T4), i.e., 12 months after the intensive intervention to investigate maintenance of the changes immediately post-intervention (T3) (see Fig. 2). In vocational schools, 14 months is the most feasible follow-up period to optimise retention of students (before graduating or changing schools): a longer time-horizon would lead to higher drop-out rates due to difficulty in reaching the students. Measurements are conducted over six batches, corresponding to 6 study cohorts (Fig. 3), to even out burden of the research team. Thus, final follow-up data will be complete in May 2017. The trial employs methods to enhance quality of measurement (e.g., careful and repeated training of assessors including simulations of student contacts, exchanging assessors between schools in the same batches).

**Fig. 2 Fig2:**
[figure not shown]
Schedule of interventions and assessments. Students: sQ1-SQ4 = Questionnaires, A1-A3 = Accelerometry measurements, G1-G6 = Group intervention sessions, B = Booster session, B1-B2 = Bioimpedance measurement, I = Interviews. Teachers: tQ1-tQ3 = Questionnaires, WS1-WS3 = Workshops for teachers

**Fig. 3 Fig3:**
[figure not shown]
Timing of data collection and (expected) sample size in each batch (*k* = student groups, *n* = individual students)

School staff usually estimate the number of students to be higher than it actually will be on the day of recruitment, meaning that not all students enlisted attend school. This is due to students being transferred to other classes, dropping out of school, or classes being scheduled for on-the-job learning period out of school, etc. Thus, if the students that are reachable have not attended the information session, the research group tries to reach them at school at least three times after this session. Despite this, not all students may be reached for information and consent forms.

#### Primary outcome measures

Objectively measured outcomes (MVPA, sedentary time, breaks in sedentary time) are based on accelerometry [32]. The 3-axial accelerometer (Hookie AM 20, Traxmeet Ltd, Espoo, Finland) has been shown to be a valid measurement tool both among adults [32] and young people [34]. The accelerometer is fixed to an elastic belt and participants are instructed to wear the belt on their hip for seven consecutive days during waking hours, except during shower and other water activities, starting from the delivery day. The accelerometers collected and stored the tri-axial data in raw mode in actual acceleration (g-units). The data is analysed in 6 seconds’ epoch length. PA was categorised into three intensity categories based on metabolic equivalents (MET): light, moderate and vigorous. Light PA is defined as activity corresponding 1.5−2.9 MET, moderate activity as 3.0–5.9 MET and vigorous activity more than 6 MET [35]. According to the definition of SB [36], time spent in sitting and reclining positions are combined to indicate SB, time standing still is analysed separately. It is possible to accurately determine whether the participant is standing, sitting or lying by applying the information from the raw data of the three measurement axes of the accelerometer. While the body position during walking is upright and the direction of Earth’s gravity vector is constant, the vertical position (angle) of the accelerometer can be identified during normal walking. This known position can then be used to recognise different body postures. In standardised conditions, standing can be separated from sitting or lying with 100 % accuracy [37]. Breaks in sedentary time are calculated on the basis of the number of lying/sitting periods ending-up with a clear vertical acceleration.

Research assistants deliver the accelerometers to the participants in schools, and they collect them the subsequent week at the school. All participants are instructed not to change their usual or intended patterns of activity when wearing the accelerometer. Self-reported PA during leisure time will be assessed using the validated NordPAQ measure [38] in the questionnaire, concerning MVPA over the previous seven days. The assessments take place concurrently in both intervention and control arms to control for the effect of weather conditions on activity. The assessors are not involved in intervening on students.

#### Other measures and materials

Table 3 shows an overview of measures among student participants with literature references. Secondary outcomes include self-reported SB, body composition, self-reported well-being, psychological variables (e. g. intention to restrict one’s SB), as well as health behaviours. Process measures include indicators of the direct behavioural predictors, i.e., the hypothesised mediators, such as PA intention, motivational regulations (self-determination theory), self-efficacy, and the use of BCTs (adapted based on an earlier study [39] and the Let’s Move It feasibility trial [20]). At T1 and T4, body composition is measured using Tanita MC-780MA bioimpedance measurement device. The questionnaire data is collected online (SurveyMonkey). Participating students complete the questionnaires in the school during a class session at T1-T4.

**Table 3 Tab3:** Summary of measures among student participants in the Let’s Move It trial

	T1	T2^a^	T3	T4
Background information, covariates	X		X	X
PA & SB behavior				
Objectively measured PA & SB *(Hookie accelerometry)*	X		X	X
Self-reported PA, SB, and interruptions in SB [38, 42–46]	X	X	X	X
Other health related outcomes/covariates				
Objectively measured body composition *(Tanita MC-780 MA)*	X			X
Self-reported health & physical fitness [47]	X		X	X
Somatic symptoms (e.g. support- and mobility organ symptoms), stress, sleep [47] (e.g. [48–50]), dietary habits [51, 52]	X		X	X
Smoking	X			X
Psychosocial correlates of PA				
Behavioural beliefs: PA outcome expectations, PA descriptive norms (peers & parents), PA injunctive norm (parents), PA intention, PA self-efficacy/perceived behavioural control [53–55]	X	X	X	X
PA autonomous and controlled motivation [56]; integrated regulation subscale [57]	X	X	X	X
Opportunities for PA (school, neighborhood, at home)	X		X	X
PA automaticity [58]			X	X
PA action and coping planning [59]	X		X	X
Big five personality traits, brief measure [60]	X			
Psychosocial correlates of restricting SB^c^				
Behavioural beliefs: SB restriction outcome expectations, descriptive (peers) & injunctive norms (peers, teachers), self-efficacy/perceived behavioural control, intention [53–55]	X	X	X	X
Automaticity [58]			X	X
Autonomous and controlled motivation [56]			X	X
Perceived teacher behavior and group climate				
Perceived teacher actions to reduce students’ sitting, Perceived opportunities for SB reduction within school^b^	X	X	X	X
Teacher sitting reduction behavior (in school classes, perceived)^b^			X	X
Teacher motivational behavior for reducing student SB (e.g. discussions on SB at home/work practice)^b^			X	X
Student group climate (acceptance & safety) [61]	X	X	X	X
Behaviour Change Technique (BCT) use (enactment fidelity items)				
PA related BCT use: Frequency-dependent BCTs, Other BCTs ^b^	X	X	X	X
SB related BCT use^b^			X	X
Intervention receipt and evaluation of programme and materials^a^				
Recalled number of intervention sessions attended^a^			X	
Intervention satisfaction^a^			X	
Evaluation of intervention provider^a^ (autonomy support) [62]		X	X	
Evaluation and use of home workout videos, workbook & website^a b^			X	
Open-ended questions on intervention^a b^		X	X	
Adverse events				
Injuries or illnesses that prevent or limit PA	X	X	X	X
Perceived harmful effects from the intervention, open-ended^a b^			X	
Injuries				X

T1 = Baseline, T2 = Mid-intervention (after 3^rd^ intervention session), T3 = Post-intervention, T4 = Follow-up (14 months); PA = physical activity, SB = sedentary behaviour

^a^ = measured only of the intervention arm participants

^b^ = Questionnaire measure developed for this study

^c^ = existing measures adapted for this target behaviour

Teacher participants fill in questionnaires at T1, T3 and T4 after students’ measurements. Questionnaires measure behaviour (use of sitting reduction strategies), psychosocial determinants and use of BCTs, perceived social support from colleagues and supervisors, and background factors. Intervention arm teachers additionally fill in short feedback questionnaires after teacher workshops.

#### Harms and adverse events

PA-related injury and other perceived unintended negative consequences are self-reported by students at T3-T4. Adverse events are also be monitored constantly by project coordinators and intervention providers, and addressed in qualitative evaluation. Prior to the start of the trial, possible scenarios of adverse events were discussed (e.g., increased incidence of sports-related injuries, body dissatisfaction leading to eating disorders or steroid use for gaining muscle mass), and the team resolved to address these potential emerging effects promptly. However, the intervention content itself aimed to prevent such harmful effects by providing exercises to improve motor skills as a means for injury prevention, and by several exercises and discussions to prevent emergence of body dissatisfaction.

#### Economic evaluation

The economic evaluation will model the potential cost-effectiveness of the intervention in increasing PA and SB. Resources relating to intervention implementation will be collected and then used to calculate the costs relating to the added value of intervention with regard to primary outcomes. As the target group is not a patient population, health-related quality-of-life questionnaires are not used nor the longer term impact on quality-adjusted life years. Cost-effectiveness will be presented as the cost per added PA minute and reduced SB minute.

#### Qualitative process evaluation

Thematic, semi-structured individual interviews are conducted among a subsample of students, to evaluate e.g. receipt of the program and student interpretations of the causal mechanisms of change. A subsample of students from the control arm are interviewed to be able to make accurate conclusions about the mechanisms and effects of the intervention. Focus group interviews are conducted among a subsample of teachers, to evaluate e.g. receipt of the teacher workshops and identify needs for improvements before possible nation-wide dissemination. All interviews are recorded and transcribed. Additionally, field notes are kept and recorded during project meetings with teachers and during visits to schools.

Data management details can be acquired from the first author.

#### Strategies to ensure maximum study participation

The standard operational procedures for research assistants collecting the data explicitly advise and script friendly and respectful treatment of the students. We also offer coffee, tea, lemonade and biscuits during the data collection. *Questionnaire data*: While the consenting students fill in the electronic questionnaires, the non-consenting students are offered an alternative task: a written essay based on a dietary self-assessment test (at T4, on PA). This essay is in line with the schools health education curriculum and ensures these students are also focused on a meaningful task during assessment in-class. *Accelerometry*: Accelerometers are delivered to students with instruction and motivation on in a carefully scripted manner (at T1, one-on-one; at T3 & T4, in small groups). To avoid forgetfulness and support participants' use of the accelerometer in the mornings and assure wear for as long as possible, SMS reminders are sent early (6.30 – 7 a.m., during the internal pilot slightly later) to participants who do not opt out from this offer. To ensure retention at T4 and adequate use of the accelerometer, a movie ticket voucher is offered to all those returning the accelerometer promptly. At T1, T3 and T4, we offer for those who are willing to receive the print-out for their use of accelerometer. *Bioimpedance*: Bioimpedance measurements are conducted by a same-sex research assistant. Feedback is offered for those interested. To guarantee correct comprehension of the print-outs (and to avoid potential unintentional side effects, e.g., body dissatisfaction), they are given to students in a one-on-one personal consultation (2–5 min) after T1. Feedback is given in an identical way in both arms.

### Statistical analyses

Effectiveness analyses will be conducted according to the intention-to-treat principle. Primary and secondary outcomes will be analysed using generalised linear mixed model (GLMM) that will allow to take into account correlations between observations. These methods also allow the incorporation of incomplete longitudinal data into the analysis. Additional sensitivity analysis using the “as treated” approach will be conducted in order to gauge efficacy. Process analyses will include e.g. multiple mediation models to test whether the impact of the intervention is explained by its effect on the hypothesised mediators. We will conduct the outcome analyses separately for gender and different levels of baseline activity. When allowed by time and funding resources, we will also conduct the analyses by educational track, parental SES, and baseline body composition. Quantitative analyses will be conducted using the R, SPSS and the Mplus statistical softwares.

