## Methods/Design

### Aims of the study

The primary aim of the trial is to determine the effectiveness of the Let’s Move It intervention on changes in students’ physical activity and sedentary behaviour over two months (post-intervention, T3) and 14 months (long-term follow-up, T4), specifically in the following primary outcome measures:Moderate-to-vigorous intensity PA (MVPA), as measured by accelerometry and self-reportSedentary behaviour: a) Sedentary time, and b) Breaks in sedentary time (accelerometry)

We hypothesise that the intervention is effective in increasing or maintaining PA and reducing SB, compared to control group, among girls and boys, both immediately and one year after the intensive intervention (i.e., 2 and 14 months from baseline).

As the trial is designed especially for adolescents with low PA at baseline, we expect to detect a significant difference in change in MVPA among students with low or moderate levels of MVPA at baseline. We also aim to examine the cost-effectiveness of the intervention, in terms of determining cost of incremental activity. Additionally, we will evaluate changes in secondary outcomes among students (e. g. other indicators of activity, body composition, physical and mental well-being, as well as psychosocial variables) and teachers. Process evaluation will be conducted to examine mechanisms of change, implementation fidelity and key components of the intervention, as well as responses and effectiveness in subgroups.

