### Participants and eligibility criteria

Participants are vocational students in study year 1 and 2 (typically aged 15–17). All students will be invited to take part. Of educational tracks, those that meet the following criteria were selected for the study: Those educational tracks whose 1) students, compared to other educational tracks in the Finnish National School Survey, report on average higher levels of SBs and 2) report lower levels of PA on their leisure-time, 3) student intake in the national system is high to meet sample size requirements, and 4) future occupations that are either sedentary or require adequate/good physical condition. These educational tracks were selected based on evidence (Finnish National School Health Promotion survey, THL) and active consultation with the study scientific steering committee and with stakeholder expert group meetings, and the educational tracks were ranked as follows: 1. Business and administration, 2. Business information technology, 3. Nursing, 4. Hotel, restaurant and catering studies, 5. Tourism, 6. Car mechanics. The final selected combination of tracks (1.-4.) allowed for an even proportion of boys and girls in the trial. Next, the eligibility criteria are explained for schools, classes, individual students, and individual teachers.

(1) **Vocational schools**. Of the vocational schools within the study region, we decided to select schools that have the highest number of starting students in selected educational tracks (to meet sample size requirements). Six school units were recruited. In these schools, the trial aims to include the maximum number of classes in years 1 and 2 in the selected educational track present in the school during the study period (and not in vocational work practice outside school).

Schools had to agree to randomisation, allow teachers to participate in the Let’s Move It workshop training, scheduling the Let’s Move It student program in their curriculum and be representative of Finnish vocational schools.

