### Sample size

The internal pilot study data (the first and second batches) were subject to interim analysis in line with the analysis plan to investigate whether the assumptions for the initial power calculations were correct (e. g., intra-cluster correlation and standard deviations for changes in outcomes). This was done in order to make adjustments to the data collection plan, to avoid collecting too much or too few data. Additionally, accumulation of accelerometry data was investigated. Altogether 502 participants (96 % of total potential) consented to the measurements. Three hundred seventy six participants were delivered the accelerometer, and of these, 267 (71 %) wore the accelerometer device over 10 h of data on at least four days. Descriptive data from the internal pilot study is presented in Additional file 2: Table S1.

We conducted power analyses for all primary outcome measures. For individual-level design, a sufficient number is 176 persons per arm to determine a change of effect size d = 0.30 (e.g. a mean of 8.24 min difference in daily MVPA or 33.44 min difference in daily sedentary time) with 80 % power and an alpha of 5 %, translating to a post-dropout sample size of 352.

Individuals in this trial are nested within clusters (classes) when the intervention is delivered, which may affect the results. Therefore we also calculated the effect of clustering on the power, with a method [33] that took into account the intracluster correlation coefficient (ICC), varying cluster sizes and the expected effect. Data from the internal pilot was used to estimate the ICC and assess the likely mean and SD of cluster sizes. The ICC for MVPA in the internal pilot study varied from 0.033 (self-report measure) to 0.059 (objective measure) and we used a mean cluster size of 17 (SD = 3.83). This resulted in design effects of 1.56 and 2.00, giving us 80 % power to detect d = 0.3 with a sample sizes of 549 and 703, for self-report and objective MVPA measures, respectively. Using the same cluster parameters for the SB measures, with ICC of 0.012 for interruptions to sitting and 0.057 for sedentary time, design effects of 1.21 and 1.96 point to requirements of 425 and 691 students, respectively.

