Drop-out rates in previous similar trials [9] with sample totalling more than 100 and containing both genders have varied widely, from 3.1 to 54.1 %. Our internal pilot study showed a dropout of ~25 % from T1 to T3. Due to improvements in follow-up data collection procedures, dropout rates are expected to diminish in batches 3–6. In conclusion, with an expected sample size of ca. 1100 students, and with a dropout of 20 % from T1 to T3 and a further 20 % from T3 to T4, we would be well-equipped to account for clustering in all primary outcome measures with the post-dropout sample size of 704. Assuming 20 % of participants are classified as high-active and therefore excluded from the MVPA analysis, we expect to achieve 93 % power to detect d = 0.3 with individual-level analyses. Due to the drop in SD, this effect translates to an absolute difference of 7.25 min for the target group, instead of 8.24 min for the whole sample. The ICC estimated from the internal pilot study for the low- to moderate-active students’ MVPA change was 0.038, leading to a design effect of 1.65 and subsequently a post-dropout sample size of 580 to reach 80 % power.

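### Outcomes are to be analysed separately for girls and boys, but the trial is not sized for either gender, and separate models cannot show whether the genders differ

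*Protocol article*

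**What the plan says.** The Aims of the study section states the hypothesis that the intervention is effective "compared to control group, among girls and boys, both immediately and one year after the intensive intervention". The Statistical analyses section then commits to the method without condition: "We will conduct the outcome analyses separately for gender and different levels of baseline activity". Three further factors are optional: "When allowed by time and funding resources, we will also conduct the analyses by educational track, parental SES, and baseline body composition".

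The Sample size section begins at the individual level, where "a sufficient number is 176 persons per arm to determine a change of effect size d = 0.30", "with 80 % power and an alpha of 5 %, translating to a post-dropout sample size of 352". It inflates this for class clustering, outcome by outcome, and concludes for the whole sample that "we would be well-equipped to account for clustering in all primary outcome measures with the post-dropout sample size of 704". It then gives the low- to moderate-active students their own ICC (0.038), design effect (1.65) and required number (580) for MVPA. No number, ICC or power is given by gender. On the gender mix, the eligibility section says: "The final selected combination of tracks (1.-4.) allowed for an even proportion of boys and girls in the trial".

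**The concern.** One sentence of the analysis section names two splits, baseline activity and gender. Baseline activity has its own sample size calculation and gender has none, although the stated hypothesis names girls and boys.

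Two things are at stake. First, a gender-specific analysis may be read as a test of the hypothesis in that gender when its power is well below that of the whole sample. Second, separate models do not address the question a reader will bring to them, which is whether girls and boys respond differently. A significant result in one gender beside a non-significant one in the other is not evidence of a difference. The Background reports that earlier school programmes changed activity mainly among girls, so a chance split in that direction could easily be taken as confirmation.

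**Working it through.** **Inputs (Sample size section unless noted).** d = 0.30; alpha 5%; 80% power; 176 per arm; mean cluster size m = 17, SD 3.83; ICC 0.059 (accelerometer MVPA), 0.057 (sedentary time), 0.033 (self-reported MVPA), 0.012 (breaks); 1100 students at baseline, with 20% lost by T3 and a further 20% by T4. An even gender mix is from the eligibility section.

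**Step 1: reproduce the plan.** A two-sided two-sample t-test at 5% with d = 0.3 and 176 per arm has 80.1% power, so the stated number matches a two-sided test. The design effect is DE = 1 + [(CV² + 1)m − 1] × ICC with CV = 3.83/17, so CV² = 0.0508. For accelerometer MVPA this is 1 + (1.0508 × 17 − 1) × 0.059 = 1.995 (plan: 2.00). The others are 1.961, 1.556 and 1.202 (plan: 1.96, 1.56, 1.21). Multiplying by 352 gives 702, 690, 548 and 423 (plan: 703, 691, 549, 425). Dropout gives 1100 × 0.8 × 0.8 = 704. The plan's figures hold. Whole-sample power at 704 is 80%, 81%, 89% and 95% in the order listed.

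**Step 2: within one gender at T4.** 704/2 = 352 students, or 176 per arm. This equals the plan's own requirement for 80% power with no clustering, so the shortfall comes from the clustering that the plan says must be allowed for. The effective number per arm is 176/DE. The gender make-up of classes is not given, so two bounds are used:
- single-gender classes (m = 17, the plan's printed DE);
- evenly mixed classes (m = 8.5, same CV and ICC). For accelerometer MVPA, DE = 1 + (1.0508 × 8.5 − 1) × 0.059 = 1.468.

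| Outcome | DE, single / mixed | Effective n per arm | Power at T4 |
|---|---|---|---|
| Accelerometer MVPA | 2.00 / 1.468 | 88.0 / 119.9 | 51% / 64% |
| Sedentary time | 1.96 / 1.452 | 89.8 / 121.2 | 52% / 64% |
| Self-reported MVPA | 1.56 / 1.262 | 112.8 / 139.5 | 61% / 70% |
| Breaks | 1.21 / 1.095 | 145.5 / 160.7 | 72% / 77% |

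**Step 3: within one gender at T3.** 1100 × 0.8 / 2 = 440 students, or 220 per arm. Power is 60-74% for accelerometer MVPA, 61-74% for sedentary time, 71-80% for self-reported MVPA and 81-85% for breaks.

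**Step 4: discordant results under equal effects.** With power p in each gender and independent results, exactly one gender is significant with probability 2p(1 − p). For accelerometer MVPA this is 2 × 0.508 × 0.492 = 0.50 (single-gender classes) or 2 × 0.638 × 0.362 = 0.46 (mixed). This counts either direction; one named direction has half that chance, about 23-25%. Girls and boys in mixed classes share class effects, and that positive correlation would lower the mixed figure somewhat.

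**Step 5: sensitivity to the gender split.** With a 40:60 split at T4, power across the four outcomes and both bounds is 42-68% in the smaller gender and 58-83% in the larger.

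**The case against.** The strongest reply is that the article never makes two confirmatory gender claims. The phrase about girls and boys can be read as describing the student population. The abstract's hypothesis does not mention gender. The Aims section and the section on secondary outcomes and process evaluation both place effectiveness in subgroups with process evaluation. The group for which the authors do expect a significant MVPA difference, the low- to moderate-active students, has its own sample size calculation. Alpha rules and subgroup details may also sit in an analysis plan that is not shown.

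Much of this stands, and it rules out several stronger readings:
- A reader might infer that each gender is tested at a full 5%. The 5% appears only in the sample size calculation. Two independent unadjusted tests would give 1 − 0.95² = 9.75% for one outcome at one time point, but nothing says the tests are unadjusted.
- A reader might say the gender analyses miss their stated 80% power. The article never states 80% within a gender, so no printed figure is wrong.
- A reader might say only the pooled sample is powered. The low- to moderate-active group is too, for MVPA.
- A reader might suspect that the optional factors will be chosen after the results are known. The article openly marks them as optional and rests no claim on them, and the analysis plan may fix the list.

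One part is not answered. Running the gender analyses separately is a method the article states, and it cannot compare the genders whatever alpha is used. Placing subgroups under process evaluation does not label gender results exploratory while the hypothesis sentence itself names both genders.

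**Conclusion.** The point holds as a mismatch between hypothesis, analysis and sizing. Girls and boys are named in the hypothesis and analysed separately, and the trial is sized for neither. At 14 months every primary outcome has less than 80% power within a gender, from 51% to 77%, against 80% to 95% in the whole sample. At 2 months the shortfall is not universal: breaks passes 80% and self-reported MVPA reaches about 80% if classes are evenly mixed. For accelerometer MVPA, close to half of trials with equal true effects would show one significant and one non-significant gender.

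These figures assume a 50:50 split, equal arms, d = 0.3 in each gender, and the whole-sample ICC and cluster-size variation carried over to each gender. The discordance figure also assumes independent results. The problem is one of interpretation and can be put right before analysis; the whole-sample calculation is unaffected.

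**What to change.** 1. State that, for the whole sample, the pooled arm contrast is the confirmatory one and that the whole-sample power applies to it. Leave the low- to moderate-active MVPA analysis as planned.
2. Replace the separate gender analyses by an arm-by-gender term in the same GLMM, keeping the class clustering. Report both gender-specific effects and the interaction, each with a confidence interval.
3. Label the gender results exploratory, and make no claim of a gender difference from within-gender p-values. Word the hypothesis to match.

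The cost is wording and one model term. The trial gives up a confirmatory claim within each gender, for which it is not sized. The interaction will also be imprecise. For accelerometer MVPA at T4, taking the genders as independent, the standard error of the difference is √(2/88 + 2/88) = 0.213 SD for single-gender classes, or √(2/119.9 + 2/119.9) = 0.183 SD for mixed classes. The 95% interval is then about ±0.42 or ±0.36 SD. A non-significant interaction should therefore not be reported as showing that girls and boys respond alike.
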